## Analysis of parameters of bone metabolism and phosphor homeostasis

The techniques for these analysis are available (mostly routine analysis and/or optimized for earlier research (f.e. FGF-23)). This part of the research project will be conducted in close corporation with [name] (Laboratory of Nefrology) and [name] (Laboratory for Experimental Medicine and Endocrinology).

## Subjects

Twenty healthy subjects will be included in a randomized cross-over study with 10 subjects in each group. Group 1 will start with the high protein diet and switch to the low protein diet. In group 2 the interventions occur in reversed order (Figure 1). After an explanation of the study and its purpose written consent will be asked (‘Informed consent’: appendix 1).

Inclusion criteria:

- Healthy subjects
- Regular dietary pattern (3 meals per day)
- Age: 18-45 years
- BMI: 18.5-27 kg/m2

Exclusioncriteria:

- Intake of antibiotics one month prior to the study
- Abdominal surgery in the past (except appendectomy)
- Intake of medication influencing the gastrointestinal system 14 days prior to the study
- Consulting a dietician
- Severe liver- or kidney failure
- Vegetarian
- Intake of pre-/probiotics
- Participation to a study using radio-activity 1 year prior to the study

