## ENDPOINTS

The primary endpoints of this study are the effects of a high, low and normal protein diet on the colonic metabolism in healthy subjects. Following parameters will be evaluated (description of used techniques, see above):

- Analysis of fat mass
- Analysis of ammonia metabolism in the colon after administration of lactose-[15N, 15N]-ureid
- Analysis of urinary p-cresol excretion as a marker of protein fermentation
- Analysis volatile organic compounds (VOC) in feces
- Analysis of genotoxicity of fecal water using the Comet Assay
- Analysis of cytotoxicity of fecal water using the WST-1 assay

The secondary endpoints of this study are the effects a high, low and normal protein diet on the phosphor homeostasis in healthy subjects. The following parameters will be evaluated (description of used techniques, see above):

- Analysis of biochemical parameters of phosphor homeostasis (serum calcium and phosphor, calcidiol, calcitriol, PTH, FGF-23)
- Analysis of parameters of bone formation and bone resorption
- Analysis of dietary phosphor and calcium
- Analysis of urinary excretion of calcium and phosphor

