## METHODS

- On day 1 of the study subjects undergo indirect calorimetry used to measure baseline energy need. The result of this measurement and information on physical activity of the subject will be used to calculate the total energy need. These measurements will be performed by Prof. [name].
- During the first week of the study, subjects can follow their normal diet, but are asked to fill in a 7-day dietary journal.
- On day 5 of the 1st week the percentage body fat is measured (impedance measurement) and a test evaluating the colonic metabolism has to be performed.
- Starting the 2nd week of the study the volunteers of group 1 receive a high protein diet during week 2 and 3 of the study, while the volunteers of group 2 receive a low protein diet during week 2 and 3 of the study.
- Three days before the end of the first intervention period (=day 19) the subjects again perform a test (impedance measurement + colonic metabolism), after which they switch diet for the next 2 weeks.
- Three days before the end of the second intervention period (=day 33) the last test is performed.
- During week 3 and week 5 the volunteers again fill in a 7-day dietary record.

Subjects maintain their normal physical activity level during the entire period of the study.

On the morning of the test subjects come sober to the laboratory Digestion & Absorption. After donating a baseline urine and blood sample and measurement of the body fat percentage, a test meal is consumed by subjects. Following this test meals urinary and fecal samples have to be collected.

- Test meal:
  - Pancake supplemented with lactose-[15N, 15N]-ureid (75 mg), a capsule containing [3H]-PEG (185 kBq) and a glass water.
- Samples:
  - Urine samples (complete collection): 48h
  - Fecal samples (complete collection): 72h

|  | Day 0 | | Day 5 | | Day 19 | | | | | | Day 33 | | |
| --- | --- | --- | --- | --- | --- | --- | --- | --- | --- | --- | --- | --- | --- |
|  | IC | | Test 1 | | Test 2 | | | | | | Test 3 | | |
|  | |  |  |  |  | |  | |  | |  | | |
| Group 1 (n=10) | | Normal diet | | High protein diet | | | | | Low protein diet | | | |  |
|  | |  | |  |  | |  |  | |  |  | | |
| Group 2 (n=10) | | Normal diet | | Low protein diet | | | | | High protein diet | | | |  |
|  | |  | |  | |  | | |  | | |  |  |
|  | | Dietary journal | |  | | Dietary journal | | |  | | | Dietary journal |  |

IC = indirect calorimetry

Test 1-3: impedance measurement + evaluation of colonic metabolism

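### The eligibility criteria screen for earlier radioactivity studies but do not exclude pregnancy or breastfeeding, although every subject takes three tritium-labelled test meals and two prescribed diets

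*Protocol*

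**What the plan says.** The Subjects section gives four inclusion and eight exclusion criteria. It asks for "healthy subjects" without defining the term, and sets "Age: 18-45 years". No criterion limits sex. The nearest medical exclusion is "Severe liver- or kidney failure". One exclusion concerns earlier exposure: "Participation to a study using radio-activity 1 year prior to the study". Pregnancy and breastfeeding are not on the list, and the protocol text available mentions no pregnancy test or contraception requirement.

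The METHODS section that holds the schedule places tests on days 5, 19 and 33, and its table note reads "Test 1-3: impedance measurement + evaluation of colonic metabolism". "On the morning of the test subjects come sober to the laboratory Digestion & Absorption", give baseline urine and blood, and then eat a test meal that includes "a capsule containing [3H]-PEG (185 kBq) and a glass water". The normal diet comes first in both groups. The high and low protein diets follow in randomized order, two weeks each.

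ENDPOINTS lists fat mass among the primary measures. The secondary measures include "serum calcium and phosphor, calcidiol, calcitriol, PTH, FGF-23", bone formation and resorption, and urinary calcium and phosphor.

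**The concern.** The protocol treats radioactivity as an eligibility matter when it looks back over the past year, but not when it looks at a possible fetus or nursing infant. The word healthy does not settle this, because a pregnant or breastfeeding woman can be healthy.

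Two things are at stake. The first is a participant safeguard that would normally stand in the criteria of a study that gives a radioactive tracer and prescribes diets. The second is interpretability. Energy need is fixed once, at the start, and both diets are built on it. Fat mass comes from impedance through equations tied to particular populations. The secondary endpoints are calcium, phosphor and bone measures. If pregnancy or breastfeeding moved any of these during the five weeks, that subject's later tests would differ from her first for a reason other than diet.

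**Working it through.** **Exposure.** Inputs: 185 kBq per test meal (METHODS and Table 1 under Dosimetry), 4.2 x 10^-11 Sv/Bq (Table 1), three tests (METHODS), and a background of 2.5 mSv/year (note to Table 1).

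- The plan's own figure: 4.2 x 10^-11 Sv/Bq x 185 x 10^3 Bq = 7.77 x 10^-6 Sv = 0.00777 mSv. Table 1 shows 0.007, which agrees by truncation; rounding would give 0.008. The table covers one administration.
- Total activity: 3 x 185 kBq = 555 kBq.
- Total dose: 3 x 0.00777 = 0.0233 mSv (0.021 mSv if the table's 0.007 is tripled).
- Share of annual background: 0.0233 / 2.5 = 0.93%.

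These figures are for the subject. Table 1 gives no separate figure for a fetus or infant. The section on colonic ammonia metabolism says that the labelled PEG is neither absorbed nor metabolized and leaves in the feces.

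**Time drift.** The documents give no size, so let d be an assumed constant change per day in some measure for one affected subject. The tests are on days 5, 19 and 33.

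| Comparison | Group 1 (high, then low) | Group 2 (low, then high) |
| --- | --- | --- |
| High minus normal | (19 - 5)d = +14d | (33 - 5)d = +28d |
| Low minus normal | (33 - 5)d = +28d | (19 - 5)d = +14d |
| High minus low | (19 - 33)d = -14d | (33 - 19)d = +14d |

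Both comparisons with the normal diet carry the drift with the same sign in either group. Randomizing the order of the two test diets cannot remove it. In high minus low, the sign depends on the group to which she is randomized, so the expected contribution is (-14d + 14d) / 2 = 0, although in the trial actually run her share is not balanced by a counterpart.

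In a simple mean over 20 subjects, one affected subject shifts a comparison with normal diet by 14d/20 = 0.7d or 28d/20 = 1.4d, and shifts high minus low by 0.7d in one direction or the other. With no affected subject, all of these are zero.

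**The case against.** The strongest reply is that the criteria state nothing false and contradict nothing; a line is merely absent, and the consent form (appendix 1), which was not available, is a natural place for a statement on pregnancy. This stands in part. A reader might infer that the study has no safeguard at all, and the documents cannot show that. What can be shown is that the list deciding who is enrolled is silent, and a statement in the consent form would still need a matching criterion.

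Three other inferences are tempting, and the documents do not support them:

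- **A material radiation hazard.** The stated non-absorption and a total of about 0.9% of annual background speak against it.
- **About ten women at risk.** That number needs the assumption that half of the 20 subjects are women, and even then it counts women, not pregnant or breastfeeding women. The protocol does not say how many women are expected.
- **Bias in high versus low protein.** With randomized order, one subject's drift has no systematic direction there.

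It is also fair to say that individual calorimetry already captures a different energy need at baseline, so only later change matters. The documents say nothing about how pregnancy or lactation affects the endpoints; that such effects exist is an assumption here. Finally, the normal diet's fixed first place exposes the comparisons against it to any time trend, whatever its cause. Pregnancy or breastfeeding is one possible source.

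**Conclusion.** The narrow point holds. As written, the criteria admit a healthy pregnant or breastfeeding woman aged 18-45 to three labelled meals and two prescribed diets. The criterion belongs in the protocol, since an analysis plan cannot screen participants.

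The consequence is modest. The exposure is 555 kBq, or 0.023 mSv to the subject on the protocol's own coefficient. The number affected is unknown and may be zero. The effect on the endpoints is unquantified and systematic only in the comparisons against normal diet. This rests on reading healthy in its ordinary sense, on the test meal being given at all three tests as the schedule indicates, and on nothing in the unavailable material amending the criteria. It is a cheap improvement to make before enrolment, and does not suggest that the trial is unsafe or its main diet comparison invalid.

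**What to change.** Add pregnancy and breastfeeding to the exclusion criteria under Subjects. State that status is confirmed before the first labelled test meal, and align the consent form with the criterion. The baseline urine already given on the test morning can serve for the pregnancy check; breastfeeding needs only a question. The first test is on day 5, before the diets start in week 2, so a volunteer found ineligible then would have received neither label nor diet.

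The cost is one line of text, a simple check on a sample already collected, and a negligible effect on recruiting 20 subjects.

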## ENDPOINTS

The primary endpoints of this study are the effects of a high, low and normal protein diet on the colonic metabolism in healthy subjects. Following parameters will be evaluated (description of used techniques, see above):

- Analysis of fat mass
- Analysis of ammonia metabolism in the colon after administration of lactose-[15N, 15N]-ureid
- Analysis of urinary p-cresol excretion as a marker of protein fermentation
- Analysis volatile organic compounds (VOC) in feces
- Analysis of genotoxicity of fecal water using the Comet Assay
- Analysis of cytotoxicity of fecal water using the WST-1 assay

The secondary endpoints of this study are the effects a high, low and normal protein diet on the phosphor homeostasis in healthy subjects. The following parameters will be evaluated (description of used techniques, see above):

- Analysis of biochemical parameters of phosphor homeostasis (serum calcium and phosphor, calcidiol, calcitriol, PTH, FGF-23)
- Analysis of parameters of bone formation and bone resorption
- Analysis of dietary phosphor and calcium
- Analysis of urinary excretion of calcium and phosphor

## DESIGN OF ADAPTED DIETS

Prof. [name] will design lists with 7 breakfasts, lunches and dinners resulting in a 9% protein intake during the low protein diet. A second set of lists will be designed resulting in a 30% protein intake during the high protein diet. These lists will adapted to the energy intake of the different subjects (f.e. by leaving out or adding a slice of bread). The subjects will be able to choose a breakfast, a lunch and a dinner from these lists.

## METHODS

- On day 1 of the study subjects undergo indirect calorimetry used to measure baseline energy need. The result of this measurement and information on physical activity of the subject will be used to calculate the total energy need. These measurements will be performed by Prof. [name].
- During the first week of the study, subjects can follow their normal diet, but are asked to fill in a 7-day dietary journal.
- On day 5 of the 1st week the percentage body fat is measured (impedance measurement) and a test evaluating the colonic metabolism has to be performed.
- Starting the 2nd week of the study the volunteers of group 1 receive a high protein diet during week 2 and 3 of the study, while the volunteers of group 2 receive a low protein diet during week 2 and 3 of the study.
- Three days before the end of the first intervention period (=day 19) the subjects again perform a test (impedance measurement + colonic metabolism), after which they switch diet for the next 2 weeks.
- Three days before the end of the second intervention period (=day 33) the last test is performed.
- During week 3 and week 5 the volunteers again fill in a 7-day dietary record.

Subjects maintain their normal physical activity level during the entire period of the study.

On the morning of the test subjects come sober to the laboratory Digestion & Absorption. After donating a baseline urine and blood sample and measurement of the body fat percentage, a test meal is consumed by subjects. Following this test meals urinary and fecal samples have to be collected.

- Test meal:
  - Pancake supplemented with lactose-[15N, 15N]-ureid (75 mg), a capsule containing [3H]-PEG (185 kBq) and a glass water.
- Samples:
  - Urine samples (complete collection): 48h
  - Fecal samples (complete collection): 72h

|  | Day 0 | | Day 5 | | Day 19 | | | | | | Day 33 | | |
| --- | --- | --- | --- | --- | --- | --- | --- | --- | --- | --- | --- | --- | --- |
|  | IC | | Test 1 | | Test 2 | | | | | | Test 3 | | |
|  | |  |  |  |  | |  | |  | |  | | |
| Group 1 (n=10) | | Normal diet | | High protein diet | | | | | Low protein diet | | | |  |
|  | |  | |  |  | |  |  | |  |  | | |
| Group 2 (n=10) | | Normal diet | | Low protein diet | | | | | High protein diet | | | |  |
|  | |  | |  | |  | | |  | | |  |  |
|  | | Dietary journal | |  | | Dietary journal | | |  | | | Dietary journal |  |

IC = indirect calorimetry

Test 1-3: impedance measurement + evaluation of colonic metabolism

Figure 1: Scheme of the study and scheduled tests

## Remuneration of the volunteer

The subjects receives 100€ for participation in the study

## Dosimetry

- The stable isotope 15N causes no radiation and is therefore completely safe
- For determination of the oro-anal transit time the radioactive isotope 3H is used. The used amount of radioactivity is very low and is much less than the allowed yearly limit of intake (ALI, IRCP-68(1994)) (table 1).

Table 1: Data related to ICRP-68 (1994) standards.

| Isotope (protocol) | Internal dose (50y) (Sv/Bq) | Administered activity (Bq) | Effective dose (50y) (mSv²) |
| --- | --- | --- | --- |
| **3H** | 4,2 x 10-11 | 185 x 103 | 0,007 |

# 1ALI=annual limit of intake

2Average natural background radiation in Belgium: 2.5 mSv/year (UNSCEAR 2000)

